#### Assessment of trial procedures

To assess the validity of key outcome measures (Objective 2.a), convergent validity of baseline proxy-reported WHODAS and CANSAS will first be determined by calculating Pearson’s correlation coefficient (*r*). Internal and external responsiveness to change from baseline to 2 and 5 months will be calculated, using proxy-reported WHODAS as an external reference measure. These steps will be repeated for the RAS-DS, using proxy-reported WHODAS as an external reference, and for RAS-DS using CANSAS as an external reference measure. Cronbach’s Alpha will be reported as a measure of internal consistency of the measures. Exploratory Factor Analysis with varimax orthogonal rotation will be conducted to identify any possible factors which the measures may load on.

To assess the feasibility of trial procedures (Objective 2.b), a meeting will be held with ASWs, the social worker, and the study coordinator to gather feedback on the feasibility of the GroupAct and fidelity checklist, e.g., time taken to rate, ease of use, usefulness in providing immediate feedback and identifying training needs. Numbers of eligible participants at each clinic will be compared to predicted numbers (*n*=14) and the proportion consenting to participate will be calculated. The proportion of, and reasons for, participants lost to follow-up at 2 months and 5 months will be recorded. At the 5-month endpoint, all control arm participants will be assessed for contamination including awareness of recovery groups, using a single item administered as the last question on the outcome evaluation assessment. In addition, IDIs will be carried out with control arm participants to gain a more in-depth understanding of extent and means of awareness of intervention groups, and potential impact of exclusion from the groups on their wellbeing (see Table 3). Outcome measure means and standard deviations will be used to inform the sample size calculations for a definitive trial (Objective 2.c).

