### Assessment of trial procedures

2.a. To establish the validity of quantitative outcome measures of recovery, unmet needs, and functioning2.b. To assess trial procedures including the acceptability and feasibility of fidelity measures, recruitment and retention rates, and the suitability of an individually randomised design2.c. To synthesise outcome data to inform the sample size of a definitive trial

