#### Recruitment

We estimate that a minimum of 15 people with psychosis access care at each participating clinic. Information leaflets and posters will be used to provide initial sensitization to the study in the clinic waiting areas. At these clinics, during all regular scheduled appointments for people with psychosis taking place during the recruitment period, psychiatric nurses will provide initial brief information about the study and ask for verbal consent for a PRIZE staff member to speak with them or contact them. The nurse will use a script to clarify that the person has no obligation to participate and that non-participation will not affect their care. Service users who agree will be directed to speak with an assessor immediately following their clinic appointment. The assessor will give initial verbal information on the study to the service user in isiXhosa and complete a screening checklist for eligibility criteria (except capacity to consent). A home visit will then be arranged for eligible service users who are interested in participating. Service users will be invited to identify a primary caregiver or a person of their choice to participate in the study and to be present at the home visit. To recruit a pragmatic and inclusive sample, service users who do not have an available caregiver will still have an opportunity to participate in the study.

At the home visit, the trial social worker will give verbal and written information on the study in isiXhosa. If the participant is interested in participating, the social worker will conduct the full capacity assessment, consent procedures, and baseline assessment. All procedures will be conducted privately. If the potential participant needs time to consider the information, a separate meeting will be scheduled within the following week. The subset of eligible but declining participants will be contacted by telephone by the study coordinator to invite them to participate in the qualitative interview.

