##### Quantitative data collection (outcome evaluation)

The following service user outcome measures will be assessed in both trial arms: functioning (self- and proxy-rated 12-item WHO Disability Assessment Schedule (WHODAS) [35, 36]), personal recovery (Recovery Assessment Scale-Domains and Stages (RAS-DS) [37]), unmet needs (Camberwell Assessment of Need Short Assessment Schedule), internalised stigma (Internalized Stigma of Mental Illness Scale (ISMI) [38]), perception of respect and value (two newly developed questions based on formative work), alcohol use (Alcohol Use Disorders Identification Test- Consumption (AUDIT-C)) [39], health service use (bespoke questions), relapse, anti-psychotic medication adherence (5-point ordinal scale). The caregiver outcome is caregiver burden (caregiving consequences of the Involvement Evaluation Questionnaire (IEQ) [40]) (Table 5). Support for recovery (Brief INSPIRE) will be assessed in intervention arm participants only, in relation to their ASW facilitator (2-month endpoint), peer facilitator (5-month endpoint), and psychiatric nurse (baseline, 2- and 5-month endpoints). All instruments have been translated into isiXhosa and back translated to English to check for semantic equivalence. In addition, cognitive interviewing has been carried out for the WHODAS, CANSAS, and RAS-DS to detect difficulties with understanding of items and response categories and translation, and amendments made accordingly to ensure content validity.

**Table 5 Tab5:** Quantitative outcome measures

Outcome	Measure	Details
Disability	Self-rated and proxy-rated 12-item WHO Disability Assessment Schedule (WHODAS) 2.0	The 12-item WHODAS 2.0 is a generic instrument for assessing disability relating to any health condition across cultures. It has been used previously in South Africa for people with severe mental illness [24]. Item-response theory-based scoring will be used to convert scores to a 0–100 scale [36]. The WHODAS proxy version has the same properties as the self-rated version but has been designed to be answered by a caregiver, relative or friend [36].

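### Objective 2.a covers self- and proxy-rated functioning, but the convergent-validity and responsiveness analyses name only the proxy WHODAS

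*Protocol article*

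**What the plan says.** In the protocol article's list of objectives, Objective 2.a reads: "To establish the validity of quantitative outcome measures of recovery, unmet needs, and functioning". The section on quantitative data collection for the outcome evaluation defines the functioning outcome in two forms: "functioning (self- and proxy-rated 12-item WHO Disability Assessment Schedule (WHODAS".

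The analysis for this objective is in the Methods section headed Assessment of trial procedures. It has these parts:

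- A baseline correlation: "convergent validity of baseline proxy-reported WHODAS and CANSAS will first be determined".
- Responsiveness: "Internal and external responsiveness to change from baseline to 2 and 5 months will be calculated, using proxy-reported WHODAS as an external reference measure". The measure under test is not named; from the context it is CANSAS.
- RAS-DS, first reference: "These steps will be repeated for the RAS-DS, using proxy-reported WHODAS as an external reference".
- RAS-DS, second reference: "for RAS-DS using CANSAS as an external reference measure".
- Cronbach's alpha, which "will be reported as a measure of internal consistency of the measures", and an exploratory factor analysis. Neither says which WHODAS form is included.

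Under Recruitment, "service users who do not have an available caregiver will still have an opportunity to participate in the study". The Sample size section bases the power for Objective 2.a on 80 retained service users: above 90% for correlations of 0.4 or more, and 70% for a standardised change of 0.28.

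**The concern.** The objective and the analysis do not cover the same ground. Self-rated WHODAS is the form of the functioning outcome that needs no second respondent, so it is an obvious candidate outcome for the definitive trial that this study is meant to prepare. Followed as written, the plan yields no convergent-validity or responsiveness evidence for it.

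The proxy form also serves as an external reference for CANSAS and RAS-DS without being compared with the self-rated form. If the correlation between CANSAS and the proxy form is low, the plan offers little to show which of the two is at fault. RAS-DS has a second reference, but that reference is CANSAS, which is itself being examined against the proxy form.

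Finally, a proxy score needs a second respondent, and the Discussion calls caregiver participation optional. Service users who have nobody to act as proxy may differ in functioning from the rest. They would be lost from exactly those analyses that use the proxy form.

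**Working it through.** **1. Which measure enters which analysis**

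| Analysis | Self-rated WHODAS | Proxy WHODAS | CANSAS | RAS-DS | Proxy score needed |
|---|---|---|---|---|---|
| Baseline correlation | no | yes | yes | no | yes |
| External responsiveness, first step | no | reference | tested (by context) | no | yes |
| The same steps for RAS-DS, first reference | no | reference | no | tested | yes, except internal responsiveness |
| RAS-DS, second reference | no | no | reference | tested | no |
| Internal responsiveness of CANSAS and RAS-DS | no | no | tested | tested | no |
| Alpha and factor analysis | not stated | not stated | yes | yes | only for the proxy form |

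Self-rated WHODAS is named in no row. It may enter the last one. No row compares the two WHODAS forms.

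**2. Reproducing the stated power**

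Inputs from the Sample size section: n=80, r=0.4, standardised change 0.28. The significance level is not given; I assume two-sided 5%.

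- Correlation, Fisher z: power = Φ(atanh(0.4)·√(n−3) − 1.96). At n=80 this is Φ(0.4236 × 8.775 − 1.96) = Φ(1.757) = 96.1%. The plan says above 90%; it agrees.
- Change from baseline: power = Φ(0.28·√n − 1.96). At n=80 this is Φ(2.504 − 1.96) = Φ(0.544) = 70.7%, or 69.6% with the noncentral t. The plan says 70%; it agrees.

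**3. How many pairs the correlation claim needs**

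The smallest n with at least 90% power for r=0.4 is 62: Φ(0.4236 × √59 − 1.96) = Φ(1.294) = 90.2%. At n=61 it is 89.7%.

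- Of 80 retained service users, 18 could lack a proxy score (18/80 = 22.5%) before the claim fails.
- At baseline, with the recruitment target of 100, 38 could lack one (38/100 = 38%).

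**4. Range over the share without a proxy score**

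The article gives no such share, so these shares are assumptions, applied to the 80 retained.

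| Without proxy | Pairs | Power for r=0.4 |
|---|---|---|
| 0% | 80 | 96.1% |
| 10% | 72 | 94.1% |
| 20% | 64 | 91.1% |
| 30% | 56 | 87.0% |
| 40% | 48 | 81.1% |

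The 70% figure for a change of 0.28 is affected only if the change score analysed is the proxy WHODAS itself. With 64 pairs it would then be 61.0%.

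**The case against.** The strongest reply is that functioning is not left out. A correlation is symmetric, so correlating proxy WHODAS with CANSAS is convergent evidence for one of the two functioning forms. An observer-rated reference for self-reported measures is also a legitimate choice, because it limits shared method variance. The article states that the proxy version has the same properties as the self-rated one, and it reports cognitive interviewing for the WHODAS. On numbers, it plans 100 service users with 100 linked caregivers and applies 20% attrition to both, which gives about 80 pairs if the two members of a pair are lost together. The primary outcomes are acceptability and feasibility, and the extra correlations could be run at any time.

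Most of this stands, and it rules out several stronger readings that a reader might infer:

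- *Self-rated WHODAS is never tested, or a third of the objective cannot be answered.* Not supported. Alpha and factor analysis may include the self-rated form, and the other form has a convergent analysis.
- *The proxy form is the reference for everything.* Not so: RAS-DS is also set against CANSAS.
- *Service users without a caregiver are dropped from the validation.* Not so: RAS-DS against CANSAS and the internal responsiveness of both need no proxy. Nor is a missing proxy score certain, since a service user may name a person of their choice and the instrument can be answered by a relative or friend.
- *The proxy form is unvalidated.* This cannot be shown from the article, because the source cited for its properties is not at hand.
- *The power statement is wrong.* It reproduces at n=80.

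The mismatch itself is not answered. A general statement about the instrument's properties does not replace a local comparison in a study whose stated purpose includes establishing validity. Nor is this detail left to another document: the article fixes the pairings and specifies the proxy form each time it uses WHODAS in them.

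**Conclusion.** The concern holds in a limited form. As written, the plan gives no convergent-validity or responsiveness result for self-rated WHODAS and no comparison of the two forms, although the objective covers functioning and both forms are collected.

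The loss of power is conditional and moderate. It depends on how many service users have no proxy score, which the article does not state. Above 90% power for r=0.4 holds with 62 or more pairs; with 40% missing among the 80 retained it would be 81.1%. These figures assume a two-sided 5% level and no allowance for clustering by clinic. The possible selective loss of people without a proxy matters more than the power. None of this touches the primary outcomes, so it is a worthwhile, cheap improvement rather than a serious defect.

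**What to change.** In the Methods section on assessment of trial procedures:

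1. Add agreement between self-rated and proxy WHODAS at baseline: intraclass correlation, mean difference and Pearson's r.
2. Name self-rated WHODAS in the convergent-validity and responsiveness steps with CANSAS and RAS-DS.
3. Show the CANSAS and RAS-DS results with the self-rated and the proxy form as references, side by side, so that service users without a proxy contribute to a WHODAS-based analysis.
4. State which WHODAS form enters alpha and the factor analysis.
5. In the Sample size section, give the expected number of service user-proxy pairs, and note that the figure of above 90% needs at least about 62 of them in any proxy-based analysis.

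Alternatively, restrict the functioning part of Objective 2.a to the proxy form and say so.

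The cost is a few more correlations on data already collected. The drawback is that measures answered by the same person share method variance, which can inflate their correlation. That is why both references should be shown and the point stated when the results are read.

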Recovery	Recovery Assessment Scale- Domains and Stages (RAS-DS)	The RAS-DS is a self-report measure of mental health recovery [37]. It includes 38 items clustered into four domains of recovery: functional recovery (“Doing things I value”); personal recovery (“Looking forward”); clinical recovery (“Mastering my illness”); and social recovery (“Connecting and belonging”). Each item is rated on a 4-point scale from 1 = “untrue” to 4 = “completely true”. “Percentage scores” are calculated for each domain and an overall score higher score represents more advanced levels of mental health recovery. It has been used previously in clinical settings in South Africa.
Unmet needs	Camberwell Assessment of Need – Short Appraisal Scale (CANSAS)	The CANSAS includes a list of 22 areas considered as potentially important needs for individuals living with mental illness. Each item is rated as either an “unmet need”; “met need” or “no need”. Percentage of unmet needs will be calculated based on number of unmet needs divided by total number of needs identified (unmet needs plus met needs). The scale has been previously used in South Africa [24].
Support for recovery	Brief INSPIRE	The brief INSPIRE assesses recovery support from a worker and has 5 items, each rated 0 “not at all” to 4 “very much”. Responses can be converted to a total score, ranging from 0 (low recovery support) to 100 (high recovery support) [41].
Internalised stigma	Internalized Stigma of Mental Illness (ISMI) Scale	The ISMI-R is a 29-item questionnaire assessing internalised stigma covering four subscales: “alienation”; “stereotype endorsement”; “perceived discrimination”; and “social withdrawal”. Items are scored on a 4-point Likert scale, from strongly disagree to strongly agree. Total scores are calculated by summing the items [38]. The scale has been previously used in South Africa [24].
Perception of respect and value	2 bespoke questions	Two questions “I feel valued and respected by my family” and “I feel valued and respected by my community” will be rated on a 4-point Likert scale, from strongly disagree to strongly agree.
Alcohol use	Alcohol use disorders identification test consumption (AUDIT-C)	The AUDIT-C includes three questions on alcohol consumption, each rated on a 0 to 4 scale. A total score can be calculated. It has been widely used and shown to be useful for assessing alcohol use in the South African context [39].

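### The exploratory factor analysis under Objective 2.a fixes an orthogonal rotation although the RAS-DS is scored as four related domains; an oblique rotation would be a minor, free improvement

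*Protocol article*

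**What the plan says.** Objective 2.a is "To establish the validity of quantitative outcome measures of recovery, unmet needs, and functioning". The section on assessment of trial procedures lists the analyses that serve it, in this order:

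- "convergent validity of baseline proxy-reported WHODAS and CANSAS will first be determined by calculating Pearson’s correlation coefficient", with the same steps repeated for the RAS-DS.
- "Internal and external responsiveness to change from baseline to 2 and 5 months will be calculated".
- "Cronbach’s Alpha will be reported as a measure of internal consistency of the measures".
- Last, "Exploratory Factor Analysis with varimax orthogonal rotation will be conducted to identify any possible factors which the measures may load on".

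No oblique alternative is named, and the instruments to be factored are not listed individually. Table 5 describes the RAS-DS: "It includes 38 items clustered into four domains of recovery". It adds that percentage scores "are calculated for each domain and an overall score". The WHODAS is described there only as a 12-item scale converted to a single 0–100 score.

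**The concern.** Varimax is an orthogonal rotation, so it fixes every correlation between factors at zero. An overall RAS-DS score on top of four domain scores is hard to justify unless the domains share something. The stated rotation excludes that shared part from the model.

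Two consequences follow. The first is certain: the factor analysis gives no estimate of how far the domains are related. The second depends on the data: if the domains are correlated, the shared variance has to appear as secondary loadings, and items that belong to one domain look as if they also belong to others.

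This matters modestly. The instruments were translated into isiXhosa, and the WHODAS, CANSAS and RAS-DS were amended after cognitive interviewing. Whether the RAS-DS keeps its structure is therefore an open question, and the factor analysis is the only listed analysis that looks at structure without taking the item-to-domain assignment as given.

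**Working it through.** **The plan's own figures.** None is given for the factor analysis. The Objective 2.a power statement in the sample size section (final n = 80) covers only correlations and sensitivity to change. It reproduces at a two-sided 5% level, which is assumed because the level is not stated:

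- r = 0.4: Φ(atanh(0.4) × √77 − 1.96) = 96%, stated as above 90%.
- Effect size 0.28: Φ(0.28 × √80 − 1.96) = Φ(0.544) = 70.7%, stated as 70%.

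Neither depends on the rotation.

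**Inputs for the check.** From the article: 38 four-point items, four domains, 100 service users at baseline (about 80 at the end). Assumed, because the article gives no values: items split 10/10/9/9, each loading on one domain only (λ = 0.65 or 0.7), and a common domain correlation ρ from 0 to 0.7. A secondary loading of 0.3 is used as the cut-off; this is a convention and is not in the protocol.

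**What varimax must do without sampling error.** With four equally correlated factors, the factor correlation matrix has eigenvalues 1 + 3ρ (once) and 1 − ρ (three times). The symmetric orthogonal solution multiplies the true loadings by the square root of that matrix:

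- secondary loading = λ × [√(1 + 3ρ) − √(1 − ρ)] / 4
- primary loading = λ × [√(1 + 3ρ) + 3√(1 − ρ)] / 4

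For λ = 0.7:

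- ρ = 0.3: secondary 0.7 × (1.378 − 0.837)/4 = 0.095; primary 0.680
- ρ = 0.5: secondary 0.7 × (1.581 − 0.707)/4 = 0.153; primary 0.648
- ρ = 0.7: secondary 0.7 × (1.761 − 0.548)/4 = 0.212; primary 0.596

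A numerical varimax search from many random starts, with the 10/10/9/9 split, gave the same averages to three decimals. Every item thus acquires three secondary loadings whose true value is zero. Sampling error then carries some of them past 0.3.

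**How many pass 0.3 in samples of this size.** Two simulations, each with principal-axis extraction of four factors:

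- A: four-category items, λ = 0.65, promax as the oblique rotation, 100 data sets per setting.
- B: continuous items, λ = 0.7, quartimin as the oblique rotation, 25 data sets per setting.

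Share of items with a false secondary loading of 0.3 or more at n = 100, varimax against oblique:

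| ρ | A | B |
|---|---|---|
| 0 | 0.3% vs 0.1% | 0.2% vs 0% |
| 0.3 | 2.0% vs 0.6% | 1.9% vs 0.1% |
| 0.5 | 12.2% vs 2.7% | 11.6% vs 0.9% |
| 0.6 | 19.1% vs 5.1% | not run |
| 0.7 | 35.9% vs 11.5% | 41.9% vs 3.8% |

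A repeat of setting A gave 9% vs 2% at ρ = 0.5 and 35% vs 11% at 0.7. At n = 80, B gave 15% vs 2% and 49% vs 9%. The mean absolute secondary loading under varimax in B was 0.107, 0.154 and 0.217 at ρ = 0.3, 0.5 and 0.7, close to the closed-form values.

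**What does not change.** Share of items whose largest loading falls on the true domain (setting A, n = 100, 60 data sets), varimax vs promax:

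- ρ = 0.3: 99.9% vs 99.9%
- ρ = 0.5: 99.6% vs 99.7%
- ρ = 0.6: 96.7% vs 97.1%
- ρ = 0.7: 92.1% vs 92.0%

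**Recovering the domain correlation.** Varimax reports 0 always. Quartimin (B, n = 100) gave means of 0.23, 0.36 and 0.48 for true values of 0.3, 0.5 and 0.7. Correlating the domain scores directly gave 0.42 and 0.59 for true values of 0.5 and 0.7, or 0.49 and 0.70 after correction for domain-level alpha.

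**The case against.** The case for leaving varimax alone is that the analysis is exploratory, comes last, and drives nothing: no item deletion, rescoring or decision rule depends on it, and the primary outcomes are acceptability and feasibility. If the aim is to see which factors the items load on, varimax places the largest loading as well as promax does. Communalities and fit do not depend on rotation, and the same extraction can be rotated again at any time. All of this stands, and it is why the point is minor.

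Three stronger readings are tempting, and the document does not support them:

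- **That the translated RAS-DS would be judged to lack its structure.** The primary-loading results contradict this; only the secondary loadings become less clean.
- **That the overall score could not be examined.** Domain scores are calculated, so they can be correlated directly, and in the simulation this recovered the true correlation better than the oblique factor correlation did. A general factor also shows in the eigenvalues under any rotation: the ratio of first to second rose from 1.2 at ρ = 0 to 3.1 at 0.5 and 5.0 at 0.7.
- **That the WHODAS score is undermined.** The article gives the WHODAS no domains. If one factor is retained, rotation does nothing.

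What remains is that a restriction at odds with the way the RAS-DS is scored has been written into the plan. Rotating again later is possible, but it would then be a change made after seeing the loadings.

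**Conclusion.** The point holds as a minor one. That the factor analysis reports no factor correlation follows from the method and needs no assumption. The inflation of secondary loadings is conditional on a domain correlation that the article does not give: negligible at 0, about 2% of items at 0.3, about 9–12% against 1–3% with an oblique rotation at 0.5, and 35–42% against 4–11% at 0.7. These figures are for n = 100 and rest on assumed loadings of 0.65 to 0.7, equal correlations between domains, items belonging to one domain only, four factors retained, and a 0.3 cut-off. They were obtained for the RAS-DS layout only; the CANSAS was not simulated.

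A reader might infer that Objective 2.a as a whole is compromised. It is not: convergent validity, responsiveness and Cronbach's alpha are independent of the rotation.

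**What to change.** In the section on assessment of trial procedures, replace the varimax orthogonal rotation with an oblique rotation (promax or oblimin), applied where more than one factor is retained. Report the factor correlation matrix beside the directly computed correlations between RAS-DS domain scores. The two should be read together, because the oblique estimate tends to fall below the true correlation at this sample size.

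The cost is one option in the Stata rotation command and one extra table. No data collection, sample size or other analysis changes. If the domains prove unrelated, nothing is lost: at a correlation of zero both rotations gave false secondary loadings in under 1% of items.

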### Study design

The design is an individually randomised parallel group feasibility trial comparing recovery groups in addition to TAU compared to TAU alone in a 1:1 allocation ratio (see Fig. 1). We will use mixed methods to address our study objectives. Data will be collected at baseline, 2 months, and 5 months post-intervention start.

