#### Sample size

We will aim to recruit a total of 100 service users and 100 linked caregivers. Assuming 20% attrition, ~40 service users and ~40 caregivers will receive the intervention and each recovery group will have a mean size of 11.4 participants (5–6 service users and 5–6 caregivers). We envisage these are sufficient numbers to adequately assess the acceptability and feasibility of the intervention (Objective 1.a), whilst accounting for potential differences in experience due to variations between clinic catchment areas, e.g. in socio-economic status, accessibility of venue, and community resources.

For the validation of outcome measures (Objective 2.a), we estimate that our final sample size of *n*=80 service users will give >90% power to detect correlations of ≥0.4 and 70% power to detect a standardised effect size of 0.28 for internal sensitivity to change at 2 months compared to baseline. The effect size of 0.28 is based on a mean change of 5 from baseline to follow-up, with a standard deviation of 15 and an intraclass correlation of 0.05. As this is a feasibility study, it is not powered to detect differences in outcome measures between treatment arms (Objective 3.a). We anticipate a total of approximately *n*=4 ASWs, *n*=7 service user facilitators, and *n*=7 caregiver facilitators will be sufficient to make an exploratory assessment of facilitator competence (Objective 1.b).

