### Assignment of interventions

The randomisation code will be generated by an independent statistician using permuted block randomisation. The randomisation will be stratified by clinic catchment area. The trial social worker will supply the study coordinator with the details of all recruited participants, including study ID. For each recruited participant, the study coordinator will determine the allocation code using the Redcap randomisation module. They will then inform the participant of the trial arm to which they have been allocated (TAU or TAU + recovery groups) by telephone. The trial social worker and assessor will be informed of the participant ID number prior to baseline data collection, but will be masked to allocation status. At the 5-month study endpoint, assessors will be asked to report whether they have been unmasked to allocation status. Data analysts will also be masked to allocation status. Due to the nature of the intervention, it is not possible to mask participants or interventionists (ASWs or social workers).

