Health service use	Bespoke questions	Questions include number, duration and reason for inpatient admissions; and number of consultations with different types of healthcare worker in the last 2 months.
Relapse	Questions on police contact & hospitalization	Relapse is defined as either of: • Inpatient admission for mental health of any duration (assessed as part of health service use) • Any type of police contact related to mental health
Anti-psychotic Medication adherence	1 question	We will use a 5-point nominal scale measuring frequency of anti-psychotic medication adherence
Caregiver burden	Caregiving consequences section of Involvement Evaluation Questionnaire (IEQ)	31-item questionnaire assessing aspects of burden for caregivers of people with severe mental illness. All items are scored on 5-point Likert scales (0 never to 4 always). Domain scores can be computed (tension & urging range 0 to 36; worrying & supervision range 0 to 24)

Quantitative data will be collected at baseline, 2 months, and 5 months post-intervention start (see Fig. 1) at the participant’s clinic or at their home, with the exception of the Brief INSPIRE. Socio-demographic data will be collected at baseline. To avoid unmasking assessors, the study coordinator will collect brief INSPIRE data by telephone from intervention arm participants. Study data will be collected and managed on Android tablets using REDCap (Research Electronic Data Capture) electronic data capture tools hosted at the South African MRC [42, 43]. REDCap is a secure, web-based software platform designed to support data capture for research studies, providing (1) an intuitive interface for validated data capture; (2) audit trails for tracking data manipulation and export procedures; (3) automated export procedures for seamless data downloads to common statistical packages; and (4) procedures for data integration and interoperability with external sources. Assessors will be trained to administer the instruments using interactive techniques including role plays. The study coordinator will oversee data collection. Attrition will be minimised through phone calls and/or text message reminders to attend data collection and in-person tracking.

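### A contamination item for control participants at the end of the masked 5-month interview discloses allocation to the assessor, a risk the protocol avoids for Brief INSPIRE

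*Protocol article*

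**What the plan says.** Under Assignment of interventions, the Protocol article says that the trial social worker and the assessor are given participant ID numbers "but will be masked to allocation status". The same section provides a check on this: "At the 5-month study endpoint, assessors will be asked to report whether they have been unmasked to allocation status".

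Under Quantitative data collection (outcome evaluation), the people who run the outcome interviews are the assessors: "Assessors will be trained to administer the instruments using interactive techniques including role plays". That section also deals with Brief INSPIRE, which is asked of the intervention arm alone. It is taken out of the assessors' hands, with the reason given: "To avoid unmasking assessors, the study coordinator will collect brief INSPIRE data by telephone from intervention arm participants".

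Under Assessment of trial procedures, contamination is measured at 5 months, within the outcome evaluation assessment: "all control arm participants will be assessed for contamination including awareness of recovery groups, using a single item administered as the last question". No other person is named to ask it, no matching item is described for the intervention arm, and nothing says whether the unmasking report comes before or after it.

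**The concern.** A masked assessor has no way to know whom to ask a question meant for one arm. Either the assessor is told the arm, or the data capture form shows the item for some participants and not for others. In both cases allocation is disclosed, because the absence of the item points to the intervention arm as clearly as its presence points to control. The protocol recognises this hazard for Brief INSPIRE and guards against it, but leaves the contamination item unguarded in the same interview.

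Three things could be affected:

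- **Masking itself**, a stated safeguard for outcomes that are self-reported or proxy-reported to an interviewer.
- **The caregiver's measures** (proxy WHODAS and IEQ), if they are collected after the service user's interview. The proxy WHODAS is also the external reference for responsiveness to change under Objective 2.a, so the exposure would reach the validation work as well as the arm comparisons.
- **The assessors' unmasking report**, if it follows the item.

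**Working it through.** There is no stated power, error rate or event figure to reproduce here. The check sets the sections side by side and sizes the group concerned.

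**Step 1: can the masking and contamination procedures both be carried out as written?**

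| Element | What the article fixes | Section |
|---|---|---|
| Assessor's knowledge of arm | Masked | Assignment of interventions |
| Who administers the instruments | Assessors | Quantitative data collection (outcome evaluation) |
| Contamination item | Control arm, last question, 5-month assessment | Assessment of trial procedures |
| Who asks the contamination item | Not stated separately, so by default the assessor | Assessment of trial procedures |
| Brief INSPIRE (intervention arm only) | Coordinator, by telephone, to protect masking | Quantitative data collection (outcome evaluation) |
| Unmasking report | 5-month endpoint, order relative to the item not stated | Assignment of interventions |

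If the assessor delivers the item to controls only, the assessor knows the arm by the end of each interview. The two procedures are compatible only if someone else asks the item, and nobody else is named.

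**Step 2: how many participants?** The inputs come from Sample size ("We will aim to recruit a total of 100 service users and 100 linked caregivers"; "Assuming 20% attrition") and Study design ("in a 1:1 allocation ratio").

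- Service users reached at follow-up: 100 × (1 − 0.20) = 80.
- Per arm: 80 ÷ 2 = 40.
- Arm disclosed by presence of the item: about 40. By absence: about 40. Total: about 80 of 80.

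**Step 3: which data can be affected?**

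- *The participant's own 5-month answers:* not affected if the item really is the last thing seen, since those answers are already recorded. No later outcome visit follows, as data are collected at baseline, 2 months and 5 months.
- *The linked caregiver's proxy WHODAS and IEQ:* affected if the same assessor sees the caregiver after the service user, assuming that the caregiver shares the service user's arm. Not affected by this route if the caregiver is seen first or by a different assessor. The article states neither order nor assessor. The reverse also holds: if caregivers are asked the item too, a service user seen second would be exposed.
- *The unmasking report:* if it is made after the item, the truthful answer is that the assessor has been unmasked, whatever happened earlier in the trial. If it is recorded for each participant before any arm-specific item reaches that pair, it keeps its meaning. The article does not say which, nor whether the report is made per participant or once per assessor. A single report at the end of data collection would necessarily follow the items.

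**The case against.** The strongest defence is placement. Putting the item last, at the last visit, looks like a deliberate protection, and for that participant's own answers it works. A reader might infer that the 5-month scores of all 80 service users are open to assessor bias through this item; the document does not support that.

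Second, a condensed article may leave form sequence to the full protocol or the case report form. This stands as far as the order-dependent harms go: nothing shown says that caregivers are seen second, that one assessor sees both members of a pair, or that the unmasking report comes after the item. It would be wrong to say that the caregiver data are biased or that the unmasking report is spoiled. It does not answer the main point, because the article itself states both the masking and the control-arm item, and states the safeguard for one arm-specific measure but not for the other.

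Third, the word *only* is not in the text. Controls only is the natural reading, but it is a reading. Nor would asking both arms repair the problem: intervention participants know of the groups, so their answers would tend to reveal their arm. For the same reason an intervention-arm rate would be no useful comparator, and its absence is not a fault.

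Fourth, the stakes are modest. The primary outcomes are acceptability and feasibility, and the arm comparisons are unpowered and reported without p values. A reader might also suppose that masking success is one of the feasibility parameters for the definitive trial. Objective 2.b does not list it; the unmasking report appears only under Assignment of interventions, with no stated analysis.

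**Conclusion.** The inconsistency is real. As written, a control-arm question sits inside an interview run by masked assessors, and on the natural reading it discloses the arm of about 80 service users (100 recruited, 20% attrition), although the protocol removes Brief INSPIRE from that interview for this very reason.

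What follows with certainty, on that reading and with the assessor asking the item, is loss of masking by the end of each 5-month interview. Bias in the participant's own recorded answers does not follow. Exposure of the linked caregiver's proxy WHODAS and IEQ, and an unmasking report that is positive by design, each follow only under an order that the document leaves open. The point deserves correction because masking is a stated safeguard and the repair is cheap; it does not threaten the primary outcomes.

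**What to change.** Have the study coordinator collect the contamination item by telephone, as already planned for Brief INSPIRE, after both the service user and the linked caregiver have completed their 5-month assessments. The coordinator carries out the allocation and tells participants their arm, so no new person is unmasked. State also that the assessor's unmasking report is recorded for each participant before any arm-specific item is asked.

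The cost is a short call to about 40 control service users, and to their caregivers if they too are to be asked, with the possibility that some are not reached by telephone. No outcome measure, sample size or analysis changes.
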